## Abstract

**Background:**

Particularly in groups of adolescents with lower educational level the smoking prevalence is still high and constitutes a serious public health problem. There is limited evidence of effective smoking cessation interventions in this group. Individualised text messaging (SMS) based interventions are promising to support smoking cessation and could be provided to adolescents irrespective of their motivation to quit. The aim of the current paper is to outline the study protocol of a trial testing the efficacy of an SMS based intervention for smoking cessation in apprentices.

**Methods/Design:**

A two-arm cluster-randomised controlled trial will be conducted to test the efficacy of an SMS intervention for smoking cessation in adolescents and young adults compared to an assessment only control group. A total of 910 daily or occasional (≥ 4 cigarettes in the preceding month and ≥ 1 cigarette in the preceding week) smoking apprentices will be proactively recruited in vocational school classes and, using school class as a randomisation unit, randomly assigned to an intervention group (n = 455) receiving the SMS based intervention or an assessment only control group (n = 455). Individualised text messages taking into account demographic data and the individuals' smoking behaviours will be sent to the participants of the intervention group over a period of 3 months. Participants will receive two text messages promoting smoking cessation per week. Program participants who intend to quit smoking have the opportunity to use a more intensive SMS program to prepare for their quit day and to prevent a subsequent relapse. The primary outcome measure will be the proportion of participants with 7-day point prevalence smoking abstinence assessed at 6-months follow-up. The research assistants conducting the baseline and the follow-up assessments will be blinded regarding group assignment.

**Discussion:**

It is expected that the program offers an effective and inexpensive way to promote smoking cessation among adolescents and young adults including those with lower educational level and independent of their motivation to quit.

**Trial registration number:**

ISRCTN: ISRCTN19739792

## Background

Tobacco use is a major cause of disease burden and the single most preventable cause of death in the world [1,2]. Although smoking prevalence rates among adolescents of most European countries have declined within the last few years, smoking continues to be a serious problem, particularly in adolescents and young adults with lower educational level [3,4].

There is limited evidence of smoking cessation interventions demonstrating efficacy in adolescents and young adults [5,6]. In a Cochrane review of smoking cessation interventions for smokers who are younger than 20 years, approaches based on the *Transtheoretical Model *[7] achieved moderate long-term success, whereas the efficacy of psychosocial and pharmacological interventions has not been demonstrated so far [5]. A recent review [6] suggested delivering (1) smoking cessation programs for youth in contexts which are geared to youth such as schools or sports clubs, (2) interventions addressing cognitive-behavioural, motivational and social influence contents, and (3) programs with at least five sessions.

Electronic communication technology such as mobile phone text messaging (SMS) has the potential to deliver smoking cessation support to large population groups. In 2010, 98% of 12-19-year-old adolescents from Switzerland owned a mobile phone; use of the mobile phone was the most frequent leisure time activity in this population group. Furthermore, reading and sending of text messages were the most frequent activities when using the mobile phone [8].

By use of expert system technology that provides information based on individual demographic or smoking-related characteristics, electronic communication technology can be a viable, time- and cost-saving alternative to interpersonal counselling [9,10]. Particularly, SMS provides opportunities for individualised and interactive information delivery that may be accessed easily, independent of time and place.

To date, two randomised controlled studies were conducted to test the efficacy of SMS based smoking cessation interventions in adults motivated to quit smoking [11,12]. Within those studies, conducted in Great Britain and New Zealand, smokers who intended to quit within the subsequent month received motivational messages and behavioural-change support over a period of 26 weeks. The messages were matched to participants' demographic and smoking-related characteristics gathered at baseline. Additionally, participants could request instant messages aimed at craving or lapse situations. Five text messages per day were sent to the participants one week before and over four weeks after a predefined quit date that was negotiated with each participant. After this period, the intervention became less intensive, with the number of messages sent being reduced from five a day to three a week until the end of the 26th week. While intention-to-treat analyses could not reveal a significant intervention effect at the 6-months follow-up in the study by Rodgers et al. [12], Free et al. [13] found significantly higher abstinence rates in the intervention than in the control group (9% vs. 4%).

Within two pilot studies in which young adult smokers, irrespective of their motivation to quit, were proactively invited to an SMS based smoking cessation intervention, high participation and retention rates could be achieved [14,15]. To date, no randomised controlled trials testing the efficacy of smoking cessation interventions employing SMS in adolescents and young adults, or trials testing the efficacy of SMS interventions in smokers irrespective of their motivation to quit, have been reported.

Our aim is to outline the study protocol of a trial testing the efficacy of an SMS based intervention for smoking cessation in apprentices, irrespective of their motivation to quit. Apprentices have been chosen as the target population since evidence revealed high smoking prevalence rates in this subgroup of adolescents and young adults with heterogeneous educational level [4,16].

## Methods/Design

### Design and hypotheses

A two-arm cluster-randomised controlled trial will be conducted to test the efficacy of a text messaging based intervention for smoking cessation in adolescents and young adults compared to an assessment only control group. Apprentices within vocational schools will be proactively invited for study participation irrespective of their intention to quit. The smoking cessation text messages will be based on the *Health Action Process Approach *(HAPA, [17]) considering cognitive-behavioural and motivational components. Text messages will be sent to the participants over a period of three months and will be tailored according to data gathered at baseline and a weekly SMS assessment. At the six months follow-up, we expect a higher 7-day point prevalence smoking abstinence rate in apprentices of the intervention group than in those of the assessment only control group. Secondary outcome measures will be 30-day point prevalence smoking abstinence rate, self-efficacy for smoking cessation, nicotine dependence, and quit attempts. An overview of the study design is presented in Figure 1.

**Figure 1 F1:**
[figure not shown]
**Study design**.

### Participant recruitment and baseline assessment

Smoking apprentices will be recruited at vocational schools in Switzerland. Contact teachers for addiction prevention in approximately 30 Swiss vocational schools will be invited to participate with some of their classes in a study testing the efficacy of a text messaging based smoking cessation program. Participating contact teachers will schedule one school hour per school class for the screening of eligibility criteria, study information, and baseline assessment. Study participants will be recruited by study assistants (graduate students of psychology). The study assistants will invite all apprentices from a school class to participate in an online health survey during a regular school lesson, reserved for health education. Furthermore, they will inform the apprentices that some persons will be invited to participate in a study testing the efficacy of a text messaging intervention for health promotion. To decrease reporting bias the study assistants will not provide more information about the purpose of the study before the screening of eligibility criteria will be completed. Afterwards the apprentices will be invited to fill in an online screening. The screening includes the assessment of demographic data, alcohol consumption, weekly physical activity, smoking status, and ownership of a mobile phone. Inclusion criteria for study participation are (1) daily or occasional cigarette smoking (at least 4 cigarettes in the preceding month and at least one cigarette during the preceding week) and (2) ownership of a mobile phone. Subsequently, eligible persons will be informed about the aim of the study, the intervention arms, assessments, reimbursement, and data protection. Study information will be provided online and in paper form by the study assistants. Reimbursement of 10 Swiss francs (~ € 8.00) for participation at the follow-up assessment after 6 months will be offered to all study participants. Reimbursement of 1 Swiss franc (~ € 0.80) will be offered to the participants of the intervention group for each SMS response to the weekly SMS assessments within the program. After receiving informed consent online, all study participants will be invited to choose a username and to provide their mobile phone number. Furthermore, the following smoking related variables will be assessed: intention to quit, daily/weekly cigarette consumption, time to first cigarette in the morning, past quit attempts, smoking status of friends and parents, and age of smoking onset.

### Ethical review

The study protocol was approved by the Local Ethics Committee of the Canton of Zurich, Switzerland. The trial will be executed in compliance with the Helsinki Declaration.

### Randomisation and allocation concealment

To avoid spill-over effects within school classes, we will conduct a cluster-randomised controlled trial using school class as a randomisation unit. Due to the heterogeneity of apprentices in the different vocational schools (e.g. concerning gender or professions), we will use separate randomisation lists for each vocational school (stratified randomisation). Furthermore, to approximate equality of sample sizes in the study groups, we will use block randomisation with computer generated randomly permuted blocks of 4 cases [18].

The study assistants supervising the baseline assessment in the vocational schools will be blinded concerning group allocation of the school classes. Also, group allocation will not be released to study participants until having provided informed consent, their username, mobile phone number, and baseline data of the above mentioned smoking-related variables. Furthermore, the study assistants conducting the computer assisted telephone interviews at follow-up will be blinded when assessing the primary and secondary outcome measures.

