#### Online assessment

Beyond the screening questions and the assessment of the above mentioned smoking related variables, which will be assessed in both study groups, participants of the intervention group will additionally receive online questions assessing (1) outcome expectancies of smoking cessation, (2) situations in which craving for cigarettes occur, (3) alternative strategies to handle these craving situations, and (4) costs per pack of cigarettes.

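### The allocation-release rule is tied to the individual participant although the whole class shares one allocation and enrols in one supervised lesson, so concealment and assistant blinding are not secured

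*Protocol article*

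**What the plan says.** All references are to the protocol article.

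- **Unit.** Under Randomisation and allocation concealment: "we will conduct a cluster-randomised controlled trial using school class as a randomisation unit". Everyone in a class therefore has the same allocation.
- **Setting.** Under Participant recruitment and baseline assessment, contact teachers "will schedule one school hour per school class for the screening of eligibility criteria, study information, and baseline assessment". Study assistants recruit during that lesson.
- **Consent.** The same section makes consent individual and places it before the contact details: "After receiving informed consent online, all study participants will be invited to choose a username and to provide their mobile phone number". The smoking-related baseline items are listed after that.
- **Release.** Back under Randomisation and allocation concealment: "group allocation will not be released to study participants until having provided informed consent, their username, mobile phone number, and baseline data". No condition concerning the rest of the class is given.
- **Assistant blinding.** Same section: "The study assistants supervising the baseline assessment in the vocational schools will be blinded concerning group allocation of the school classes".
- **Arm-specific questions.** Under Online assessment, "participants of the intervention group will additionally receive online questions assessing" four further topics. The section does not say when or where these are asked.

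**The concern.** A release rule that looks only at the participant's own progress suits individual randomisation. In a class-randomised trial the first disclosure in the room discloses the arm of everyone in the room. If it happens during the lesson, a slower classmate may decide on consent, or answer items such as intention to quit, already knowing the arm. The assistant who is recruiting and supervising may know it too.

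Apprentices would have reasons to react. Before consenting they are told about the arms and the reimbursement. Only the intervention group earns 1 franc per weekly SMS reply, which over three months is roughly 12 to 13 francs on top of the 10 francs offered to everyone for follow-up. Smokers are invited whether or not they wish to quit, so some may be drawn to the intervention and others put off by it. Consent given with the arm known can make the arms differ in who joins. Randomising classes does not protect against this, and adjusting for measured baseline variables corrects it only in part.

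**Working it through.** **1. The plan's own figures.** The Sample size calculation gives 25% versus 17%, two-sided alpha 5% and 80% power.
- The chi-square formula without continuity correction gives 406 per group, as stated.
- Average cluster size: 20 × 0.35 = 7.
- Design effect: 1 + (7 − 1) × 0.02 = 1.12.
- 406 × 1.12 = 454.7, rounded up to 455 per group and 910 in total.

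These reproduce, and this point disputes none of them.

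**2. What one disclosure reveals.** With 7 participants per class, one early release reveals the allocation of 7 − 1 = 6 others on average. About 910 / 7 = 130 classes are involved. The figure of 6 counts classmates who share the allocation. It does not count classmates who have yet to consent, and the documents give no figure for those.

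**3. The order of steps.** Screening comes first, then study information, consent, username and phone number, and the smoking items. Release may follow at any time after that. For consent to be affected, one apprentice must complete the whole sequence while another is still deciding. For baseline answers to be affected, the other need only still be answering. The Discussion puts baseline assessment and program registration together at about ten minutes. Nothing in the text makes classmates move in step, and nothing makes the system wait for the slowest.

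**4. Whether in-lesson disclosure is likely.** The Online assessment section presents the intervention-only questions as additional to the screening and smoking items that both groups answer, and those items belong to the lesson. The article describes no separate later session. In-lesson disclosure is therefore the natural reading, but it is not stated.

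**5. Illustration of possible bias (assumed inputs only).** Suppose a share f of would-be control participants decide after a leak, and a proportion c of those decline because of it. The loss is L = f × c. If the decliners would have had abstinence q, the control rate shifts by (0.17 − L × q) / (1 − L) − 0.17.

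| f | c | L | Controls left of 455 | Shift if q = 9% | Shift if q = 34% |
|---|---|---|---|---|---|
| 0.25 | 0.05 | 0.0125 | 449 | +0.10 points | −0.22 points |
| 0.50 | 0.10 | 0.05 | 432 | +0.42 points | −0.89 points |
| 0.75 | 0.20 | 0.15 | 387 | +1.41 points | −3.00 points |

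The planned difference is 8 points. The sign depends on who declines. If the decliners were in intervention classes instead, the effect on the between-arm difference would reverse. None of f, c or q is in the documents, so the table shows only that the direction is open and that the size runs from negligible to material.

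**The case against.** The strongest objection is textual. A reader might infer that each apprentice is shown the arm on completing baseline. The wording says only that release does not come earlier than that. Release after the whole class has finished, or after the lesson, fits it equally well. The time and place of the intervention-only questions are also unstated. This stands, and it is why the point is conditional.

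A second objection is that screen timing is an operational detail which an article leaves to the full protocol. This carries less weight. The article does state a release rule and an assistant-blinding claim; the weakness is that the rule is set at participant level, which does not by itself support the claim.

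Three stronger inferences are also tempting and are not supported:

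- **That nearly all classmates would consent knowing the arm.** Consent comes early in the sequence, and many may have consented before anyone finishes. Eligibility on smoking is settled earlier still, at screening.
- **That the bias favours the intervention by a calculable amount.** This needs refusals in one arm only and an assumed abstinence rate among refusers. The documents support neither. Intention to quit is recorded at baseline in both arms and Data analyses allows covariate adjustment, so there is some partial protection.
- **That blocks of 4 within school make later classes predictable.** Of the six possible 2:2 orders, two fix two positions from the earlier ones and four fix one, a mean of (2 × 2 + 4 × 1) / 6 = 1.33 of 4. Using this requires the in-lesson leak, knowledge of the block boundaries and knowledge of the earlier classes' arms. The article does not say that one assistant covers successive classes in a school.

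**Conclusion.** The point holds in conditional form. The release safeguard is conditioned on the individual, the allocation belongs to the class, and no class-level hold is stated. If the arm or the arm-specific questions appear when an individual finishes, pre-consent concealment for slower classmates and the stated blinding of the supervising assistant can both fail within the lesson. One disclosure would reach 6 classmates on average at the planned cluster size. The number still undecided, and the size and direction of any bias, cannot be determined from the documents.

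The conclusion rests on classmates working at their own pace in a shared room, which follows from individual online consent in one lesson. It also rests on in-lesson disclosure being possible, which the text allows but does not assert. The blinding of the telephone interviewers at follow-up is a separate provision and is not affected. Because the remedy costs almost nothing and secures two safeguards that the article already claims, it should be made before recruitment starts.

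**What to change.** State, and program into the online system, that release is by class. The allocation and the intervention-only questions are withheld until every eligible classmate present has either declined, or consented and completed baseline. Alternatively, both are sent after the lesson. If this is already the practice, one clarifying sentence is enough.

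The cost is a short wait for early finishers, or, with release after the lesson, completion of the extra questions outside it, which some may not do. The software change should be small because enrolment is already online and the program is automated, though the article does not cost it. The sample size and the analysis are unchanged.

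Asking the extra questions in both arms is not a suitable substitute. Intervention elements lists the online assessment as the first component of the program, and the Intervention section says that controls receive none of the components, so this would give controls part of the intervention.

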### Sample size calculation

Based on results of a similar study which tested the efficacy of proactive telephone counselling for smoking cessation in high school students [19], we expect an 8% difference in 7-day point prevalence abstinence rates between the intervention and the control condition at 6-months follow up assessment (25% versus 17%, respectively). A sample size of n = 406 in each study group would have 80% power for a Chi-Square Test (*α *= 5%, 2-sided) in order to detect this difference based on a calculation using *G-Power*. As apprentices are nested within school classes, we additionally needed to consider a potential design effect of 1.12 (assumed class size: 20 apprentices; 35% study participants resulting in an average cluster size of n = 7; intra-cluster correlation coefficient: 0.02) resulting in a required sample size of n = 455 per study group and a total of N = 910 study participants.

### Intervention

#### Technological background

The intervention program named SMS-COACH is fully automated and based on Internet technology using a LAMP system (Linux, Apache, MySQL, and PHP). The program used in the present study is an extended and modified version of a previous text messaging program for smoking cessation which was successfully tested in 2 pilot studies [14,15]. All incoming and outgoing text messages will be automatically recorded. Incoming messages will be analysed immediately 24 hr/day.

#### Theoretical background

Primarily, the program is based on the HAPA [17]. This health behaviour model suggests a distinction between motivation processes resulting in goal setting (people in this stage are called preintenders) and volition processes leading to the actual health behaviour. The latter is further subdivided into those people being inactive (intenders) and those who already adopted the health behaviour (actors). Within the initial preintentional stage, outcome expectancies (pros of stopping smoking and cons of further smoking), risk perception, and perceived self-efficacy are seen as important social-cognitive predictors in order to develop an intention to act. Within the subsequent intentional stage, planning processes are crucial in order to achieve the desired action. Once an action has been initiated, self-regulatory skills are important, e.g. how to cope with craving situations, in order to maintain the health behaviour. Beyond the HAPA we integrated intervention elements derived from the *Social Norms Approach *[20] as well as implementation intentions, which are if-then plans that link situational cues with responses that are effective in attaining a desired outcome [21].

#### Intervention elements

The intervention program consists of (1) an online assessment of the individual smoking behaviour and smoking related attitudes, (2) a weekly SMS-assessment of smoking-related target behaviours, (3) two weekly text messages tailored to the data of the online and the SMS-assessments, and (4) an integrated quit day preparation and relapse prevention program.

